## Abstract

**Background:**

There is an urgent need for evidence on how interventions can prevent or mitigate cancer-related financial hardship. Our objectives are to compare self-reported financial hardship, quality of life, and health services use between patients receiving a financial navigation intervention versus a comparison group at 12 months follow-up, and to assess patient-level factors associated with dose received of a financial navigation intervention.

**Methods:**

The Cancer Financial Experience (CAFÉ) study is a multi-site randomized controlled trial (RCT) with individual-level randomization. Participants will be offered either brief (one financial navigation cycle, Arm 2) or extended (three financial navigation cycles, Arm 3) financial navigation. The intervention period for both Arms 2 and 3 is 6 months. The comparison group (Arm 1) will receive enhanced usual care. The setting for the CAFÉ study is the medical oncology and radiation oncology clinics at two integrated health systems in the Pacific Northwest. Inclusion criteria includes age 18 or older with a recent cancer diagnosis and visit to a study clinic as identified through administrative data. Outcomes will be assessed at 12-month follow-up. Primary outcomes are self-reported financial distress and health-related quality of life. Secondary outcomes are delayed or foregone care; receipt of medical financial assistance; and account delinquency. A mixed methods exploratory analysis will investigate factors associated with total intervention dose received.

**Discussion:**

The CAFÉ study will provide much-needed early trial evidence on the impact of financial navigation in reducing cancer-related financial hardship. It is theory-informed, clinic-based, aligned with patient preferences, and has been developed following preliminary qualitative studies and stakeholder input. By design, it will provide prospective evidence on the potential benefits of financial navigation on patient-relevant cancer outcomes. The CAFÉ trial’s strengths include its broad inclusion criteria, its equity-focused sampling plan, its novel intervention developed in partnership with clinical and operations stakeholders, and mixed methods secondary analyses related to intervention dose offered and dose received. The resulting analytic dataset will allow for rich mixed methods analysis and provide critical information related to implementation of the intervention should it prove effective.

**Trial registration:**

ClinicalTrials.gov NCT05018000. August 23, 2021.

## Administrative information

Note: the numbers in curly brackets in this protocol refer to SPIRIT checklist item numbers. The order of the items has been modified to group similar items (see http://www.equator-network.org/reporting-guidelines/spirit-2013-statement-defining-standard-protocol-items-for-clinical-trials/).

## Introduction

### Background and rationale {6a}

As costs of cancer care in the USA have risen over time [1, 2], so has the burden of out-of-pocket (OOP) costs [3, 4] and indirect costs such as travel, employment changes, and caregiver costs [5–8]. These cumulative costs pose increased financial risk for people diagnosed with cancer. Despite a patient’s health insurance status, financial hardship from cancer care is prevalent: 47–49% of cancer survivors report financial hardship and 12–62% of cancer survivors report debt due to treatment costs [9]. Financial hardship is associated with decreased treatment initiation and adherence [10, 11], poor symptoms and quality of life [12, 13], and increased mortality risk [14], so preventing or mitigating its effects is a clinical imperative.

Integration of cost of cancer care information into conversations between patients and clinicians can optimize medical decision-making and reduce the risk of financial hardship [2, 15, 16], and is consistent with high-quality cancer care [17, 18] and patient preferences [19–24]. Patient understanding of OOP costs can assist with planning and budgeting and can facilitate early connection with financial support services that may help to mitigate the financial burden of cancer care [25, 26]. Yet, less than one in five patients report having cost discussions [11, 17, 27]. Consequently, many patients are uninformed about the costs of their cancer care [20] and face unexpected OOP costs [28], with important consequences for material (e.g., debt), psychological (e.g., cost-related distress), and behavioral (e.g., treatment adherence) financial hardship [9, 29–31].

There is an urgent need for evidence-based interventions on how to prevent or mitigate financial hardship for people with cancer [32, 33]. While the extent of financial hardship as a toxicity of cancer care is increasingly well-documented, there is limited evidence to date as to what types of interventions can mitigate or prevent financial hardship due to cancer care. Policy-, societal-, and organizational-level interventions, such as those focused on bending the curve of rising health care costs or improving price transparency to ordering providers are all needed, but these may take a long time or show limited effect [9, 29–31]. In the meantime, patients continue to need assistance navigating, managing, and anticipating out-of-pocket costs, and patient- and team level-interventions such as the Cancer Financial Experience (CAFÉ) study intervention may hold promise for this purpose.

An increasing body of observational evidence suggests that communication about financial concerns and out-of-pocket (OOP) costs early in the treatment trajectory and in partnership with the care team could help to prevent or lessen financial hardship. This type of communication could be delivered through patient navigation programs and is consistent with both patient and care team preferences. However, to date, there is no evidence from randomized trials about whether financial navigation during the active treatment period reduces financial hardship. Further, no intervention-based studies have provided evidence on the most effective ways to mitigate cancer-related financial hardship.

### Objectives {7}

Our specific objectives are:Objective 1: Compare self-reported financial hardship between patients receiving a financial navigation intervention versus a comparison group at 12-month follow-up.Objective 1a: Compare self-reported health-related quality of life between patients receiving a financial navigation intervention versus a comparison group at 12-month follow-up.Objective 2: Compare health service use between patients receiving to a financial navigation intervention versus a comparison group at 12-month follow-up.Objective 3: Assess patient-level factors influencing variability in dose of a financial navigation intervention.

Our primary hypotheses are that the financial navigation intervention will be associated with improved health-related quality of life and reduced financial distress at 12 months.

Analyses for objectives 1 and 2 will assess the impact of the CAFÉ intervention on the primary outcomes of cancer-related quality of life and financial distress (Aim 1) and on health services use (Aim 2).

Analysis for Aim 3 will also include assessment of the incremental benefit of extended proactive intervention (3 cycles) compared to brief proactive intervention (1 cycle).

### Trial design {8}

The CAFÉ study is a multi-site randomized controlled trial (RCT) with individual-level randomization (Fig. 1). The study has three arms: enhanced usual care (Arm 1); brief intervention (Arm 2); and extended intervention (Arm 3).

**Fig. 1 Fig1:**
[figure not shown]
CAFÉ study design overview

The intervention to be studied is a financial navigation intervention. Participants will be offered either brief (one financial navigation cycle, Arm 2) or extended (three financial navigation cycles, Arm 3) financial navigation. The intervention period for both Arms 2 and 3 is 6 months.

The comparison group (Arm 1) will receive enhanced usual care, defined as usual care plus a mailed financial resource sheet describing local and national organizations that serve people with cancer and may address financial concerns.

The original planned study was a clinic-level RCT with stepped wedge design. However, this design could be compromised in the case of COVID-19 related clinic closures, and other COVID-19 related time-trends affecting clinical care. Switching from the clinic-level stepped wedge design to an individual-randomized 3-arm trial protects against these threats to study validity. In addition, we adapted the CAFÉ intervention to be delivered remotely (phone), rather than at in-person visits, further protecting against COVID-19-related changes to clinical care. We chose a 3-group design to assess the impact of the study intervention at two different offered doses (Arms 2 and 3).

## Methods: participants, interventions, and outcomes

### Study setting {9}

The setting for the CAFÉ study is the medical oncology and radiation oncology clinics at two integrated health systems: Kaiser Permanente Washington (KPWA) in Seattle, WA, and Kaiser Permanente Northwest (KPNW) in Portland, OR. We partnered with oncology leadership and business services in both regions to implement the study.

### Eligibility criteria {10}

Inclusion criteria:KPNW and KPWA members with a new cancer diagnosis (within the past 120 days from identification date)18+ years of age (based on age at time of identification date by the study eligibility program)Visit to CAFÉ clinic/department within two weeks of identification dateCurrent, living member as of identification dateContinuous enrollment at least 6 months prior to identification dateEnglish speaker for KPWA; English or Spanish speaker for KPNW

Exclusion criteria:On do-not contact or no chart review listCancer diagnosis is for non-melanoma skin cancerCancer diagnosis is for a benign or in situ tumorHospice encounter in past yearSelf or household member has already enrolled or completed participation in CAFÉ pilot study or main trial.Unable to complete survey

### Who will take informed consent? {26a}

Trained study staff will conduct oral consent and administer the baseline survey by phone, ideally in the same conversation.

### Additional consent provisions for collection and use of participant data and biological specimens {26b}

This trial does not involve collecting biological specimens for storage.

## Interventions

### Explanation for the choice of comparators {6b}

We selected “enhanced usual care” following consultation with both health system and clinical partners as the comparison group. This was to ensure all participants at both study sites receive some information resources about available financial support services. This takes the form of a brief print resources listing available KP and external resources who provide financial resources support to people with cancer. All participants in the study have access to usual care services within the health plan in the form.

### Intervention description {11a}

CAFÉ is a financial navigation intervention designed to provide proactive, personalized, and ongoing support and referrals, including the facilitation of estimates of out-of-pocket costs for the current treatment episode. Several preliminary studies by our study team helped inform the intervention components [25, 26, 34–37]. Further, we conducted a brief pilot of the intervention in 2020, which led to the addition of hospice care as an exclusion criterion, minor adjustments to the study REDCap database, and clarification of recruitment, withdrawal, and intervention procedures.

Broadly, a CAFÉ financial navigator provides support and resources to people with cancer during active cancer treatment. Specifically, the CAFÉ navigator provides the following intervention components: (1) assessment of patient financial concerns according to one or more expected navigation pathway. These pathways are informed by our preliminary work [25] and include acute financial need or inability to pay for household expenses, deciding between care options depending on cost, and uncertainty around out-of-pocket costs and/or when patients will need to pay. (2) Proactive, personalized support, referrals, and navigation to internal and external resources as needed to resolve financial concerns.

The proposed mechanisms of action for financial navigation to influence the outcomes of cancer-related financial hardship and health-related quality of life include:Increased affordability of cancer care through connection with financial assistance, payment plan, selection of more affordable treatment plan, and/or increased understanding of upcoming out-of-pocket costsPatient has a more patient-centered experience and improved trust with health care system

We developed this novel, intervention building on pilot work and human-centered design methods in partnership with the participating oncology clinic staff and leadership and KPNW and KPWA business services. CAFÉ is founded on the model of patient-centered communication in cancer care (Fig. 2). We chose this conceptual foundation because of the inherent information-exchange function of cost of care communications, rather than a focus on health-related behavior change inherent to other theoretical models. Further, this model provides pathways through which communication can influence health outcomes, either directly through the provision of information and support that can lead to improved health outcomes, or indirectly through trust- and relationship-building and decision satisfaction [38–40].

**Fig. 2 Fig2:**
[figure not shown]
CAFÉ study conceptual model

### Intervention administration

All CAFÉ intervention activities will be administered by trained study interventionists (CAFÉ navigators. Intervention activities will be administered by phone with secure message or mail follow-up.

Intervention conditions include:Arm 1 (Enhanced usual care): Mailed financial resource sheet; no contact from CAFÉ navigatorsArm 2 (Brief intervention, 6 months duration): Arm 1 activities plus one study-initiated financial navigation cycle, participant- or clinician-initiated navigator services available, closure contactArm 3 (Extended intervention, 6 months duration): Arm 2 activities plus 2 additional study-initiated financial navigation cycles (3 total), participant- or clinician-initiated navigator services available, closure contact

One intervention cycle of financial navigation is defined as the following (the duration of each cycle is expected to vary according to participant concern):Financial concerns assessment visit proactively initiated by financial navigator to assess participant’s financial questions and concerns related to cost of carePersonalized resources and referrals specific to participant concerns identified during visitOngoing proactive navigation to provide follow-up around any concerns identified during the visit; expected to vary according to participant needsThe end of a cycle will be determined by the CAFÉ navigator, who will record in the study REDCap database.

Participant-initiated or clinician-initiated navigation: During the 6-month intervention period, care teams and participants randomized to Arm 2 and Arm 3 are encouraged to contact the CAFÉ navigator directly as needed during the 6-month intervention period.

Closure contact: Participants in both Arm 2 and Arm 3 will receive a final outreach from the CAFÉ navigator at the end of the 6-month intervention period to inform the participant that their participation in the intervention has concluded. Navigators will attempt to reach the participant by phone; if not reached, the navigator will mail a closure letter.

Coordination with care teams: CAFÉ study investigators worked closely with oncology and health system operations and business leadership at both study sites to design and launch the intervention. Study investigators made presentations to site oncology care teams before the trial launch, and created and shared a one-page information sheet about the trial in the format of “huddle cards” used in typical current practice at both sites.

To maintain communication, CAFÉ navigators inform each intervention participant’s care team via secure staff message of the participant’s participation in the CAFÉ study (Arm 2 or Arm 3). The care team is invited to contact the navigator on behalf of the study participant’s care at any time during the 6-month intervention period.

At the close of each participant’s intervention period, the CAFÉ navigators communicate intervention closure to the participant’s care team via secure EHR message.

### Criteria for discontinuing or modifying allocated interventions {11b}

Participants are free to withdraw from participation in the study (both intervention and outcome assessments) at any time upon request. Participants or relatives/caregivers can inform either the CAFÉ navigators or call the study team as provided in the study information sheet. In this instance, all data flow will stop for that participant (survey assessments, EHR), but data collected will be retained.

The date and reason for participant discontinuation of intervention activities or withdrawal from the study and date of withdrawal will be recorded on the study REDCap database.

Participants who provide consent and are randomized, and subsequently withdraw, or are discontinued from the study, will not be replaced.

A participant will be considered lost to follow-up if we cannot reach them for the final survey assessment. The study team will attempt to contact the participant up to 5 times over 30 days, leaving up to 3 messages, before assigning the participant as lost to follow-up. For participants lost to follow-up, the study team will retain EHR and survey data.

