### Strategies to improve adherence to interventions {11c}

CAFÉ navigators make up to 6 call attempts to reach a participant for each assessment visit, then send an “unable to reach” letter with our contact information and encouragement for them to reach out if they are still interested in participating.

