### Methods in analysis to handle protocol non-adherence and any statistical methods to handle missing data {20c}

The investigators and data managers will monitor data collection process on a weekly basis and ensure a minimal amount of loss to follow-up in the study. All analyses will be conducted following a modified intent-to-treat approach, including all individuals randomized regardless of their engagement with, or exposure to the intervention. Individuals with missing outcome data will not be included in the primary analysis. We will conduct an analysis assessing factors related to missing outcome assessment. We will fit logistic regression models with missing primary outcome (yes/no) as the binary outcome in the logistic regression model, and baseline characteristic variables as independent variables, to determine predictors for missingness. Baseline covariates that are significantly (at 0.10 significance level) associated with missingness from this model will be adjusted in all models to ensure the validity of a missing-at-random (MAR) assumption. If loss to follow-up is above 15%, we will employ appropriate statistical techniques to address missing data issues. We will consider multiple-imputation analyses, or inverse probability weighting to account for missingness.

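### A request to leave the study ends passive EHR capture as well as surveys, with no lesser option described, so EHR secondary outcomes are lost even for withdrawers who would have allowed capture

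*Protocol article*

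**What the plan says.** Section {11b} of the Protocol article defines withdrawal broadly: "Participants are free to withdraw from participation in the study (both intervention and outcome assessments) at any time upon request". A request may go to either of two places: "Participants or relatives/caregivers can inform either the CAFÉ navigators or call the study team as provided in the study information sheet". The consequence for data is then fixed: "In this instance, all data flow will stop for that participant (survey assessments, EHR), but data collected will be retained".

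The same section names a narrower event when it lists what goes into the database: "The date and reason for participant discontinuation of intervention activities or withdrawal from the study and date of withdrawal will be recorded". No data rule follows for someone who discontinues only the intervention.

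Loss to follow-up is a third state with its own definition, "A participant will be considered lost to follow-up if we cannot reach them for the final survey assessment", and its own rule: "For participants lost to follow-up, the study team will retain EHR and survey data".

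Section {20c} describes a modified intent-to-treat analysis, "including all individuals randomized regardless of their engagement with, or exposure to the intervention", and then leaves out participants whose outcome is missing. Its missingness model has the missing primary outcome as its dependent variable. Multiple imputation or inverse probability weighting is considered if loss to follow-up exceeds 15%.

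**The concern.** The EHR secondary outcomes in Table 1 are treatment initiation and time to it, use of medical financial assistance, total out-of-pocket expenditure and account delinquency. They come from administrative systems and need no contact with the participant. Someone who is tired of phone calls or surveys may have no objection to their continued collection. As written, the rule gives that person only one way to leave the study, and it shuts off this source too.

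Two things follow. Data that could have been kept are lost, although the analysis aims to include everyone randomised. The loss could also depend on arm. Arm 1 receives a mailed sheet and no navigator contact, whereas in Arms 2 and 3 "CAFÉ navigators make up to 6 call attempts to reach a participant for each assessment visit", and a navigator is one of the two recipients of a withdrawal request. If withdrawal differs by arm and withdrawers differ in outcome, the Aim 2 comparisons are biased. In addition, a 12-month spending total or delinquency record that stops at the withdrawal date covers less than a year, and section {11b} keeps the partial record without saying so.

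**Working it through.** **The plan's own figures.** 370 x 0.80 = 296, and 296 / 3 = 98.7, about 99 per arm. The detectable standardised difference is (1.960 + 0.842) x sqrt(2/99) = 0.398, stated as 0.40. Then 0.40 x 2.4 = 0.96 and 0.40 x 5.0 = 2.0, as stated. With 99 per arm, the power for 35% v 17.6% is 79.9%. The detectable differences (pooled variance, no continuity correction) are 17.4 points at 35% and 11.5 points at 15%, against 17.4 and 11.4 stated. The design figures reproduce.

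**Which missing-data provisions reach the EHR outcomes.** Three states have to be told apart in section {11b}:

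- Left the study on request: surveys and EHR capture stop, and earlier data are kept.
- Lost to follow-up: not reached for the final survey, and EHR data are kept.
- Intervention discontinued only: recorded, with no data rule.

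The missingness model and the 15% trigger in section {20c} are both tied to the final survey. They pool people in the first state, who lack later EHR data, with people in the second, who have it. Neither describes missingness in the EHR outcomes.

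**Contact by arm.** At up to 6 attempts per visit, the ceiling is 6 x 1 = 6 calls in Arm 2 and 6 x 3 = 18 in Arm 3 for protocol visits, and none in Arm 1. Table 2 puts the second and third Arm 3 visits at days 91 and 150. A withdrawal then comes after the day 90 EHR point and costs only 12-month outcomes.

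**Size, by assumption.** The article gives no withdrawal rate, so these are scenarios. Let w be the share withdrawn in an arm (w0 in Arm 1, w1 in one intervention arm), 35% the true event rate in both arms, and q the event rate among withdrawers, the same in both arms and varied from 0 to 70%. The rate among those who remain is (0.35 - w x q) / (1 - w). For example, with w0 = 0.02, w1 = 0.10 and q = 0, this is 0.35/0.98 = 0.357 v 0.35/0.90 = 0.389, a difference of 3.2 points with no true effect. With q = 0.70 it is 0.336/0.98 = 0.343 v 0.280/0.90 = 0.311, or -3.2 points.

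| Withdrawn, Arm 1 v intervention arm | Spurious difference, q from 0 to 70% | Relative risk | Detectable difference at 35%, 80% power |
|---|---|---|---|
| 0% v 0% (full capture, 123 per arm) | 0 | 1.00 | 15.8 points |
| 2% v 5% | +1.1 to -1.1 points | 1.03 to 0.97 | 16.1 points |
| 2% v 10% | +3.2 to -3.2 points | 1.09 to 0.91 | 16.3 points |
| 5% v 15% | +4.3 to -4.3 points | 1.12 to 0.87 | 16.6 points |

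With equal withdrawal and equal q the spurious difference is zero. If all of the 20% attrition also removed EHR data, the detectable difference would be 17.5 points.

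**The case against.** The strongest reply is about scope. The all-stop rule applies to people who ask to leave the study, including its outcome assessments, and honouring that with a full stop is a legitimate choice. A reader might infer that anyone who merely wants the calls to end loses all data. The article does not say so: it lists discontinuing the intervention as a separate event, and non-responders to navigator calls get a letter, not a withdrawal. What stands is that this separate event has no data rule and that no intermediate option is described. A fuller protocol or the consent script may offer one, but the text shown states an all-stop rule.

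A reader might also infer that the loss falls mainly on Arms 2 and 3. Navigator contact makes that possible, but there are no withdrawal figures, any participant can call the study team, and support could equally improve retention. Nor is a bias that reverses with handling supported. It would need withdrawers to be coded as non-users, whereas section {20c} excludes missing outcomes and section {11b} keeps events already recorded.

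The data are recoverable only from withdrawers who would agree to continued capture. It is also fair to say that early withdrawers lack the 12-month survey and so enter the missingness model, whose predictors are adjusted for in all models. That helps with measured baseline predictors. It does not restore the data or address missingness that depends on arm.

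**Conclusion.** The point holds as a modest, avoidable weakness in the EHR-based secondary outcomes. The rule and the absence of a lesser option are on the page, and the exclusion in section {20c} then removes these participants from the affected comparisons. Loss of precision is minor: 15.8 to 16.1-16.6 points. Bias arises only if withdrawal is unequal or selective. Under the assumed rates of 2-5% v 5-15% and a 35% event rate, it is at most about 1 to 4 points, in a direction that cannot be known beforehand. These sizes rest entirely on assumed withdrawal and event rates. Participants lost to follow-up keep their EHR data, so only explicit withdrawers, an unknown part of the 20% attrition, are concerned. The primary outcomes are survey-based and are not affected by the EHR part of the rule. This is a cheap improvement, not a threat to the trial's main conclusion.

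**What to change.** In section {11b}, replace the single all-stop rule with three recorded levels:

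- (a) Stop navigator contact only. The 12-month survey and EHR capture continue.
- (b) Also stop surveys. EHR capture continues.
- (c) Stop all further data collection, when the participant asks for that.

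Ask each participant which level is wanted, whoever takes the request, and report the levels by arm. For level (c), treat 12-month EHR totals as incomplete from the withdrawal date, not as full-year values.

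The cost is a short IRB and consent amendment, one added REDCap field and a slightly longer withdrawal conversation. Anyone who wants a complete stop still gets one.
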